# **1.0 Background and Hypotheses**

## **1.1 Disease Background**

Dementia is an age-related disease caused by neurodegeneration and characterized by progressive cognitive decline that interferes with independent living. The resulting loss of functional independence and reduced quality of life places substantial monetary demands on the individual and the public health system [1]. In the United States alone, the total monetary cost of dementia in 2015 was estimated to be $226 billion [2]. Further calculations suggest that the aging U.S population will result in an 80% increase in total societal costs by 2040 [3]. Worldwide, the prevalence of age-associated cognitive decline and dementia is also steadily increasing. With the rising population of older adults, the number of people with dementia is projected to double every 20 years, reaching 65 million by 2030 and 115 million by 2050 [4].

Although there are many causes of dementia and a wide spectrum of severity, the core clinical criteria for all-cause dementia involves cognitive or behavioral symptoms that interfere with the ability to function at work or at usual activities [5]. These symptoms are generally disclosed to clinicians through complaints from the patient or a knowledgeable informant. Further evidence for longitudinal cognitive decline can be detected though poor performance that exceeds normal age-related declines on objective assessments. Although cognitive symptoms are the hallmark of dementia, behavioral and psychological symptoms such as apathy, depression, and anxiety often dominate both the presentation and course of disease [6]. These symptoms can occur across all stages of dementia with fluctuating prominence. Meanwhile, functional abilities decline in a direct downward trajectory, limiting performance in basic activities of daily living (ADLs) that are essential for independent living. Whether cognitive impairment causes physical impairment, or other dementia-related factors drive functional decline is debatable [7, 8]. Regardless, dementia places considerable strain on patients as well as their families because they require daily caregivers. About 75% of dementia patients are cared for by family or friends at home [9]. In the U.S. in 2014, family members and friends provided 17.9 billion hours of unpaid care to dementia patients, a contribution valued at more than $217 billion [2]. In addition to unpaid hours, caregiver burden has direct impact on the caregivers’ lives, including declines in health and social life [10].

Cognitively normal older adults and patients with mild cognitive impairment (MCI) can exhibit early signs of these symptoms [11], with the exception of functional impairment [12, 13]. Importantly, cognitive and neuropsychiatric alterations are detectable even before the MCI stage [14], highlighting the important distinction between risk factors for dementia and early manifestations of the disease. Indeed, because dementia is not a specific disease but an overall term that describes a wide range of symptoms, there is no clear distinction between its causes and effects. For example, two of the top five most important risk factors for dementia, depression and low cognitive activity, are also symptoms [15]. What is clear is that the risk of dementia increases dramatically once an individual has transitioned to MCI [16]. For example, in the Cache County Study [17] 46% of patients with MCI progressed to dementia within three years, compared to 3.3% of individuals with no history of MCI. Therefore, the most promising strategy to reduce the incidence of disease may be to target modifiable risk factors in seemingly healthy older adults.

With the population of older adults expanding worldwide, and the concomitant rise in cognitively impaired individuals, the above findings highlight the importance of developing interventions to maintain or enhance cognitive function during aging. Current guidelines provide pharmacologic and non-pharmacologic recommendations for symptom management [18, 19]. However, the impact of certain medications on cognition and global functioning is modest and arguably impractical [20, 21]. Furthermore, there are currently no disease-modifying treatments or cures, despite decades of research [22]. Often irreversible brain tissue damage and loss occurs before patients present to clinic with demonstrable cognitive dysfunction [23, 24]. Therefore, successful treatment likely requires presymptomatic neuroprotective therapies [25], as opposed to disease reversal.

Vascular cognitive impairment and dementia (VCID) refers to all forms of cognitive disorder associated with cerebrovascular pathologies. VCID therefore has similar etiologies as stroke, including hypoperfusion, small vessel disease, brain hemorrhage, cerebral infarction, large-artery atherosclerosis, and cardioembolism [26]. Vascular dementia is the second most common form of dementia after Alzheimer’s disease [27], and the prevalence of milder forms of vascular cognitive impairment not qualifying for dementia is even higher [28]. This relationship between vascular disorders and cognitive decline is recognized as a top research priority in all national plans to address dementia [29]. The resulting development of imaging-based biomarkers (such as advanced arterial spin labeling magnetic resonance techniques) and improved understanding of underlying physiological mechanisms has set the stage for promising clinical investigations [30, 31]. The most effective strategy for preventing vascular-related dementia, and to some extent all forms of dementia, may be to target the underlying risk factors for cerebrovascular disease [32, 33].

## **1.2 Exercise and the Brain**

Exercise is a promising strategy to slow or prevent the progression of cognitive decline and dementia [34]. Numerous epidemiological studies indicate that engagement in physical activity improves cognitive function and reduces the risk for dementia. For example, increased physical activity in subjects without neurodegenerative disease predicts a 28% lower risk of developing dementia and a 35-38% reduced risk of cognitive decline [35, 36]. Not only is physical inactivity a top risk factor for dementia [15], but exercise and increased physical activity significantly reduce key cardiovascular risk factors that are associated with dementia [37]. Understanding the neural and physiological processes that underlie these protective effects is essential for the prescription of individually-tailored treatment strategies to promote cognitive health during aging [38].

There are two main exercise modalities: aerobic training (AT) in which large muscles move in a rhythmic manner for sustained periods, and resistance training (RT) which causes muscles to work or hold against an applied force or weight [39]. Most randomized controlled trials (RCTs) investigating effects on the brain have focused on AT. AT has been demonstrated to improve cognitive function and increase brain volume in regions known to be susceptible to age-related brain atrophy [40-42].

As mentioned above, cerebrovascular dysfunction contributes to, and may precede, neuronal dysfunction and cognitive impairment during normal aging and in patients with neurological disorders [43]. An important indicator of preclinical dementia, cerebrovascular function is associated with, and modified by, levels of physical activity [44], making it an important target for therapeutic exercise interventions. Higher levels of self-reported physical activity are associated with improved cerebrovascular structure and function [44, 45]. Cerebrovascular plasticity has been demonstrated after 12 weeks of AT through increased resting cerebral blood flow (CBF) in the hippocampus [46], associated with changes in maximal aerobic capacity, cognitive function, and gray matter volume [47]. Improvements in CBF may therefore predict exercise-induced neuroplasticity and cognitive enhancement. CBF is also negatively associated with markers of endothelial dysfunction in older adults [48], suggesting that improved systemic vascular health may mediate the link between exercise, fitness, and benefits to brain function. This idea is consistent with the theory that vascular senescence may be a common link between declines in cerebral, cardiac, and muscular structure and function with aging [49].

Although RT is recommended for older adults by the American College of Sports Medicine and American Heart Association for its putative role in the protection against sarcopenia [39, 50], its effects on the brain have been less-well studied. Thus, further investigations are needed to understand how RT impacts cerebrovascular health and cognition. Promising cross-sectional evidence supports the efficacy of RT. For example, muscle mass and strength are associated with global cognition [51, 52] and cardiovascular disease risk factors [53, 54], independent of cardiorespiratory fitness. In addition, a recent study by Xu and colleagues [55] indicates that older women who engage in RT at least once per week have greater cerebrovascular perfusion than women who do not. These studies suggest that increased muscle mass, strength, and resting CBF are potential mechanisms by which RT can attenuate or even reverse age-related declines in cognitive function. Exercise intervention studies are necessary to test and extend these observations.

Evidence from RCTs also support the efficacy of RT. Compared to AT, RT has similar, but independent effects on cognition [56-58], cardiovascular risk factors [59], and systemic vascular function [60, 61]. Therefore, RT may impact cognition through vascular mechanisms similar to that of AT. RT may also, however, provide unique benefits to the brain. One meta-analysis found that RT has a larger effect size on executive function (0.53) than AT (0.41), and that this effect size is comparable to that of combined training (0.59) [41]. Unlike AT, RT-induced cognitive enhancement is not associated with changes in aerobic capacity (maximal oxygen uptake), but rather is mediated by increases in muscular strength [62, 63]. These findings support and extend epidemiological literature linking strength with rate of cognitive decline and incident dementia [64]. However, data to support the independent relationship between physical function and cognitive decline are lacking. Further differences between these exercise modalities have been found in imaging studies. While AT-induced improvements in cognitive function are most notably associated with increased hippocampal volume [42, 65], RT-induced improvements are associated with expanded gray matter in the posterior cingulate [66]. RT has also been demonstrated to reverse the progression of white matter hyperintensities [66, 67], an imaging marker of cerebrovascular disease. These studies support the potential for RT to improve cerebrovascular function. However, further investigations are necessary to test this role of RT and determine the mechanisms linking adaptations in strength and cognition after RT.

Another mechanism by which exercise affects the brain is through neurotrophic factors. RT promotes different neurotrophic factors than does AT [68], which may contribute to their distinct physiological pathways of cognitive enhancement. Most studies that investigate the molecular basis of exercise and the brain have been performed after an acute exercise bout. Still, there is ample evidence to suggest that chronic exercise training alters resting serum levels of specific markers. Levels of brain derived neurotrophic factor (BDNF) are lower in frail older adults and patients with neurological disorders than in healthy controls [69, 70]. Both AT and RT have been demonstrated to increase resting BDNF in older adults [71], a putative marker for adult neurogenesis [72]. However, animal studies suggest that AT primarily modulates BDNF/TrkB and beta-CaMKII (calcium/calmodulin-dependent kinase II) pathways, while RT acts on the IGF-1/IGF-1R (insulin-like growth factor/receptor) and AKT pathway [68]. IGF-1 is a primary mediator for the effects of RT on muscle mass, but also passes through the blood brain barrier to stimulate neurogenesis and angiogenesis [73]. Vascular endothelial growth factor (VEGF) also helps regulate basal and exercise-induced angiogenesis [74]. In two human studies, AT did not increase resting BDNF, IGF-1, or VEGF [75, 76]. However, one study found that increased temporal lobe functional connectivity was associated with increased BDNF, IGF-1, and VEGF in the AT group and may be augmented by greater baseline VEGF [75]. The second study found that changes in IGF-1 were positively correlated with changes in hippocampal volume and memory performance [76]. These relationships were independent of fitness, perfusion, or their changes after training, suggesting that changes in IGF-1 levels over time are independently linked to hippocampal volume changes and hippocampus-dependent memory changes. Because RT increases circulating IGF-1 significantly more than AT [77], growth factor response may contribute to the distinct benefits of RT [56]. However, additional research is required to determine the contribution of molecular mechanisms to RT-induced brain adaptations.

## **1.3 Expertise and Qualifications**

Recommendations for strength development include using high loads (≥85% 1RM) for low repetitions (≤6 for core exercises) in two to six sets [78]. In addition, a progressive application of overload is essential to provide the stimulus and recovery necessary to produce optimal results [79]. Recent studies in our lab further demonstrate that short rest interval lengths augment the acute testosterone response to resistance exercise and maximize the gains in muscle size and strength after 12 weeks of periodized strength RT in older adult men [80, 81]. We have established the feasibility of applying a 12 week periodized RT protocol with high compliance rates (complete at least 31 out of 36 sessions plus pre- and post- testing) to healthy older adults (100%) and cancer patients (98.3%) in the Clinical Exercise Research Center (CERC) [80, 82]. We now aim to apply this protocol to a study of brain function in healthy older adults. Magnetic resonance imaging (MRI) and cognitive testing will be performed before and after the intervention, along with previously-used tests of physical function, body composition, and blood draws.

MRI will be performed at The Center for Image Acquisition (CIA) at Stevens Hall for Neuroimaging. The CIA has standard imaging protocols for brain morphometry, resting state brain activity, and cerebral perfusion, including the use of structural MRI, functional MRI (fMRI), and arterial spin labeling (ASL) MRI. Our collaborators at the Laboratory of Neuro Imaging (LONI) have demonstrated the feasibility of conducting an exercise intervention study that includes cognitive testing and MRI in older adults [83]. Furthermore, they have recently developed advanced ASL techniques to non-invasively measure resting CBF, arterial transit time (ATT), and intracranial vascular compliance (VC) [84, 85]. ATT, the duration for blood to travel from large arteries to capillaries, is estimated from multi-delay pseudocontinuous ASL [86]. Obesity (body fat percentage and body mass index) and poor cognitive performance have been found to be inversely related to ATT in patients with coronary artery disease [87]. In addition, by synchronizing ASL with the peak systolic and early diastolic phases of the cardiac cycle, vascular compliance can be calculated as the ratio of the change in cerebral blood volume (CBV) between systole and diastole to the change in arterial blood pressure between systole and diastole [84]. Using this technique, older adults had significantly lower intracranial VC (due to both reduced change in CBV and increased pulse pressure) than young adults. In addition, VC was strongly associated with age, CBF, and aortic stiffness.

The promise of an exercise intervention extends beyond the target disease, having further benefits to the well-being of patients. These types of treatments positively impact fundamental processes of aging, thus reducing the rate of all-cause mortality. Compared to pharmacological treatments, exercise is available at low cost and minimal risk of inducing adverse side effects. Even with moderate benefits to a specific disease like dementia, the global impact on healthcare would be substantial.

## **1.4 Hypotheses**

1. 12 weeks of periodized RT with short rest intervals improves cerebrovascular function (resting CBF, ATT, and intracranial VC) in healthy older adults 60-80 years of age.
2. A 12-week periodized RT program designed specifically to maximize strength gains improves cognition in healthy older adults.

# **2.0 Objectives and Purpose**

We propose a mechanistic proof-of-concept intervention to investigate the effects of periodized resistance training (RT) on brain health and the underlying vascular processes that mediate cognitive enhancement in older adults. The overall goal of this proposal is to apply a 12-week periodized RT program that we have previously demonstrated to optimize strength gains in older adults to a collaboration with the Laboratory of Neuro Imaging (LONI) at the University of Southern California to determine the effects on brain health in older adults. Arterial spin labelling (ASL) magnetic resonance imaging (MRI) and the NIH Toolbox® Cognition Battery will be used to assess cerebrovascular function and cognition before and after a 12-week periodized RT program in 23 healthy older adults 60-80 years of age. Participants will serve as their own controls in an initial 12-week control period, and henceforth will all receive 12 weeks of supervised RT.

To address this goal, we propose the following aims:

## **2.1 Primary Objective**

To determine whether 12 weeks of periodized RT improves cerebrovascular function in healthy older adults. Cerebrovascular function will be evaluated by resting CBF, intracranial vascular compliance, and arterial transit time (ATT), assessed using ASL MRI techniques. This study will establish response variance and effect sizes while generating preliminary signals of efficacy in an aging related outcome.

## **2.2 Secondary Objective**

To examine the effects of periodized RT on cognition in healthy older adults. The NIH Toolbox® Cognition Battery will be administered to assess executive function, attention, episodic memory, language, processing speed, and working memory. In addition to the individual measure scores, this battery will yield the following summary scores: cognitive function composite score, fluid cognition composite score, and crystalized cognition composite score.

## **2.3 Exploratory Objectives**

1. To determine whether changes in cerebrovascular function mediate the relationship between RT and improvements in cognition.

2. To evaluate intervention effectiveness and explore potential mechanisms of benefit using various physical, physiological, and biochemical outcomes. These outcome measures include: 1) physical capacity (muscle strength and maximal oxygen consumption), body composition, and functional mobility; 2) putative blood markers of exercise-induced brain plasticity (i.e. BDNF, IGF-1, and VEGF); 3) cardiovascular risk factors (i.e. blood pressure) and markers of endothelial dysfunction (i.e. tissue plasminogen activator (t-PA) and Von Willebrand factor (VWF)); and 4) brain morphology (e.g. volume, cortical thickness, and white matter lesions) and resting state brain activity.

3. To investigate associations between brain adaptations and potential mechanisms of benefit. Changes in the above outcome measures will be examined for their roles in mediating RT-induced changes in cognition and cerebrovascular function.

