# **6.0 Randomization Scheme**

No randomization will be necessary. Participants will serve as their own controls, and therefore will all receive supervised RT. The 12-week control period will be done before the RT intervention to ensure that results are not confounded by a detraining effect. In addition, long-term cognitive benefits after exercise interventions have been found up to two years follow-up [88, 89].

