# **13.0 Statistical Considerations**

## **13.1 Statistical Analysis Plan**

Participant characteristics will be described at baseline. Continuous variables will be examined for normality and described by either means and standard deviations or medians and interquartile range (if not normal); categorical variables will be described with N (%) of each category. Participant characteristics will be compared with missing data and attrition to determine if there are any systematic patterns that should be adjusted for in secondary analyses; any difference with p < 0.25 will be used in secondary analyses to see if there is an effect on the intent-to-treat model.

Comparison of cerebrovascular function (Hypothesis 1) and cognition (Hypothesis 2) between groups will follow intent-to-treat models using longitudinal linear mixed effects modeling to assess the change in these outcomes, with the main factor of period – control versus RT. The stratifying factor of gender will also be included in the model, as is standard. This same modeling will be used to test whether cerebrovascular function mediates the effect of group assignment on cognition by adding cerebrovascular function to the model of cognition and examining the change in the beta coefficient of group (exploratory objective 1). A change in beta coefficient of >20%, will be considered indicative of mediation. Because these data will be preliminary, the primary endpoint will be the effect size calculated from the estimated marginal means of differences in the change by period from the models. This can then be translated more directly into potential clinical effect.

This same modeling technique will be used for outcomes defined in exploratory objective 2. To assess the association of changes in cerebrovascular function and cognition with other outcomes (exploratory objective 3), Spearman correlations of change in outcomes, adjusted for baseline level will be computed for the total group, and stratified by group assignment.

All analyses will be performed with SPSS (v.24).

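### Exploratory objective 3 states a mediation aim, but its only assigned analysis is a correlation of changes, which can support a statement about association and not one about mediation

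*Protocol*

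**What the plan says.** Section 2.3, item 3, has two sentences. The first is an association aim: "To investigate associations between brain adaptations and potential mechanisms of benefit". The second goes further: "Changes in the above outcome measures will be examined for their roles in mediating RT-induced changes in cognition and cerebrovascular function". The measures concerned are those of item 2: strength and aerobic capacity, body composition, mobility, blood markers, blood pressure, and brain morphology and resting activity.

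Section 13.1 treats the three exploratory objectives differently.

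- **Objective 1** (does cerebrovascular function mediate the effect on cognition?): the candidate mediator is added to the mixed model and the change in the coefficient is inspected. The rule is "A change in beta coefficient of >20%, will be considered indicative of mediation".
- **Objective 2** (did each measure change?): "This same modeling technique will be used for outcomes defined in exploratory objective 2". That is the mixed model "with the main factor of period – control versus RT".
- **Objective 3**: "Spearman correlations of change in outcomes, adjusted for baseline level will be computed for the total group, and stratified by group assignment".

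Nothing in 13.1 links the objective 2 period effects to the objective 3 correlations. The design has one group: "Participants will serve as their own controls, and therefore will all receive supervised RT" (Section 6.0).

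**The concern.** Mediation of an RT effect by a marker needs two links: RT changes the marker, and that change carries through to the outcome. A correlation of two change scores across people addresses neither the first link nor the size of any effect passing through the marker. The protocol itself treats mediation as more than correlation, since it writes a separate procedure for objective 1, but it does not extend that procedure to objective 3.

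The trial describes itself as mechanistic. Objective 3 covers a long list of measures in about 20 people. If the results are read as item 3's second sentence invites, a marker could be put forward as a mechanism without RT having altered it. A marker that RT raised in everyone could be set aside.

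**Working it through.** The plan gives no figure for this analysis. Its one power figure (d = 0.611, Section 13.2) concerns a difference between dependent means. It reproduces (two-sided paired t, N = 23: power 0.7996) but does not bear on this point.

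**1. The RT effect drops out of the within-period correlation.** For person i in the RT period, let marker change be M = α + u and outcome change be Y = β + v, where α and β are the mean effects. Ranks do not move when a constant is added, so the Spearman correlation of M and Y equals that of u and v for any α, including α = 0. Adjusting for baseline does not restore α.

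**2. Marker unaltered by RT (α = 0), changes correlated for other reasons.** The assumed input is the correlation r of the two changes. Share of simulated trials with p < 0.05, n = 20:

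| r | Spearman significant |
|---|---|
| 0 | 5% |
| 0.3 | 23% |
| 0.4 | 38% |
| 0.5 | 57% |

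With adjustment for both pre-intervention levels, in a three-visit model sharing 30%, 40% or 50% of visit-level variance, the shares are about 15%, 25% and 40%. At an assumed r of 0.6, the baseline-adjusted correlation is significant in 72% (n = 20) to 78% (n = 23) of trials. The marker's own period test is then significant in only 5%.

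**3. Marker raised equally in everyone.** Assume a rise of 1 with noise SD 0.5, and an outcome rise of 0.8 with SD 1. Within the RT period the correlation is significant in 5% of trials, which is chance. This is the extreme case. In a similar model with error SD 0.7, a true-response SD of 0.8 brings detection to 63% to 70%.

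**4. Total group read as both periods pooled.** With equal numbers of control and RT changes, the shifts add αβ/4 to the covariance and α²/4 and β²/4 to the variances. With the values of step 3:

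r = (1 × 0.8/4) / √[(0.25 + 0.25)(1 + 0.16)] = 0.20 / 0.762 = 0.26.

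Simulated rank correlations average 0.28 and are significant in 40% to 45% of trials (n = 20 to 23). This is not evidence of mediation: data in which marker and outcome rise for unrelated reasons follow the same distribution. For the unaltered marker of step 2 at r = 0.6, pooling gives 94% to 96%.

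**5. Which contrasts exist.**

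| Place in protocol | Blood draw | Physical function |
|---|---|---|
| Section 9.4 | not covered | baseline, post |
| Section 9.5 | baseline, post | not covered |
| Section 16.1 | two draws: baseline, post | not covered |
| Section 3.0, Visit 6 | also pre-intervention | also pre-intervention |
| Section 9.10 (Testing Part 2 in week 15) | also pre-intervention | also pre-intervention |

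Under 9.4, 9.5 and 16.1 these measures have one change per person, spanning control and RT together. A control-versus-RT contrast then cannot be formed for them.

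**6. Would a significance gate on the period effect help?** Take a marker rise of 1 and change-error SD 0.7, so a visit-error variance of 0.49/2 = 0.245. With independent visit errors, the contrast post − 2 × pre + baseline has variance 6 × 0.245 = 1.47. The standardized effect is 1/√1.47 = 0.82, and power at n = 20 is 94%. It falls to 83% with a response SD of 0.8. At a standardized contrast of 0.4, power is only 40%.

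**The case against.** Several parts of the defence stand.

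- **Association is also an aim.** Item 3's first sentence asks for associations, and Spearman correlations serve that. The gap lies in the second sentence only.
- **Objective 2 already tests whether RT altered each marker.** A reader might infer that the plan would never notice an unaltered marker. It would; what is missing is an instruction to read the two results together.
- **No rule names a mechanism.** For objective 3 the correlations are simply to be computed, with no significance threshold. A reader might infer that any significant correlation will be reported as a mechanism, but the protocol does not say so. The percentages in the working describe what a p < 0.05 reading would do.
- **Missing a uniform riser is not a general property.** It holds for the RT-period correlation. It does not hold for a total-group correlation pooled over both periods, where the problem is that shared period shifts produce correlation.
- **The shared-variation premise is uncertain.** Cognition and MRI belong to Testing Part 1; blood, strength and body composition belong to Part 2, a separate visit. This weakens the case for influences specific to one visit. Slower influences such as health or activity could still act on both, but their size is unknown.

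The defence leaves one thing unanswered: the second sentence promises an examination of mediating roles, and the assigned method cannot deliver it.

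**Conclusion.** The point holds as a mismatch between a stated aim and its assigned analysis. Step 1 is exact and rests on no assumed variance: the RT effect on the marker does not enter the within-period correlation. The frequencies in steps 2 to 4 are illustrations under assumed values. For an unaltered marker they run from 5% with no shared variation to 72% to 78% at r = 0.6, and the documents do not say where in that range the trial would fall.

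The consequence is limited to what may be concluded from exploratory objective 3. The primary and secondary results are untouched, and the correlations remain useful as description.

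**What to change.** 1. In Section 2.3, item 3, replace the mediating-roles wording with *examined for association with changes in cognition and cerebrovascular function*.
2. In Section 13.1, state that a correlation of changes is not evidence of mediation, and that a null correlation is not evidence against it.
3. In 13.1, replace group assignment with period, and state which change intervals the total-group correlation uses.
4. Report each RT-period correlation beside the control-period correlation and beside that marker's objective 2 period effect with its 95% interval. Describe a marker as a candidate mechanism only in the light of both. Do not make significance of the period effect a condition: at about 20 people it would discard modest real effects (40% power at a standardized contrast of 0.4).
5. Before this, reconcile Sections 9.4, 9.5 and 16.1 with Section 3.0 (Visit 6) and Section 9.10 on whether blood markers and physical function are measured pre-intervention. Where they are not, state that no control-versus-RT contrast is available.

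The cost is wording in 2.3 and 13.1, plus the schedule reconciliation. The period models are already planned. The downside is that fewer markers can be called mechanisms.
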